### Control group

Participants randomised to the control group will receive TAU in accordance with national and regional guidelines which includes antidepressant medication and psychological treatments in first-hand and physical activity as an alternative [10]. The psychological treatments recommended is cognitive behavioural therapy and interpersonal therapy in first-hand and short-term psychodynamic therapy as an alternative. Treatment could vary between general practitioners and PHCs as the guidelines only provide recommendations.

## Outcome measures

### Baseline

Data will be collected four times, starting with the baseline assessment (Fig. 1). The baseline assessment will include cognitive testing, self-administrated questionnaires, and a structured psychiatric interview. All assessors (study psychologist or study physician) will receive a 1-day training on the assessment procedures and instruments. The battery of questionnaires was tested in a focus group consisting of four individuals ≥ 65 years. Their feedback was used to further enhance the feasibility and layout of the questionnaires without violating the instruments original design.

**Fig. 1 Fig1:**
[figure not shown]
SPIRIT flow diagram: schedule of enrolment, interventions, and assessments

Global cognitive status will be measured using the Mini Mental State Examination [46] – Swedish revision, MMSE-NR3, a 30-point cognitive screening test. Executive functioning will be measured with the Frontal Assessment Battery – Swedish version, FAB-SWE [47], a 6-item screening test with scores ranging from 0 to 18.

### Primary outcome

The primary outcome is depressive symptoms measured with the Montgomery-Åsberg Depression Rating Self-rating Scale, MADRS-S [48]. The MADRS-S is a nine-item questionnaire designed to measure depression severity during the past 3 days.

### Secondary outcomes

The secondary outcomes include depression diagnosis, activity level, and self-rated anxiety, daily functioning, quality of life, self-efficacy, and loneliness.

The Mini International Neuropsychiatric Interview (MINI 7.0.0) [49] is a structured psychiatric interview that will be used to assess psychiatric diagnoses, including depression diagnosis, and comorbidity at baseline. The depressive episode module in MINI 7.0.0 will be conducted by telephone to assess depression diagnosis at post-treatment and 6-month follow-up. The section for antisocial personality disorder will be excluded due to irrelevance to the current study. Depressive symptoms will be measured using the Geriatric Depression Rating Scale 15-item short form (GDS-15) [50]. This questionnaire is used to identify depression in older individuals with scores ranging from 0 to 15, with higher scores indicating more depressive symptoms Anxiety symptoms will be measured with the Geriatric Anxiety Scale – 10 item version, GAS-10 [51], with a score ranging from 0 to 30. The respondents rate their anxiety symptoms on a 4-point scale, with higher scores indicating higher levels of anxiety.

Self-rated avoidance and activation will be measured using the Behavioural Activation for Depression Scale—Short Form (BADS-SF) [52], a 9-item scale with scores ranging from 0 to 54, with higher scores indicating a higher degree of activation and lower degree of avoidance. This instrument was developed specifically to measure activation level during BA treatments.

Subjective feelings of loneliness and social isolation will be measured using the UCLA Loneliness Scale version 3 (UCLA-LS 3) [53], a 20-item scale with scores ranging from 20 to 80 points. Higher scores indicate higher degrees of loneliness. There is data supporting the reliability and validity of using the UCLA-LS 3 in assessing loneliness in a variety of populations, including older adults [53].

Physical activity level will be measured by using the Frändin/Grimby activity scale, in which people estimate their activity on a 6-point scale [54]. The scale has been shown to be valid for assessing physical activity among older adults [54, 55]. The participants will also be instructed to wear the ActiGraph GT3X + accelerometer on an elastic belt around their waist for seven consecutive days, all waking hours (except when bathing or showering). The ActiGraph GT3X + accelerometer measures movement (acceleration) in up to 3 orthogonal axes via electrical impulses. The ActiGraph (Pensacola, Florida) accelerometers are widely used in research because they have shown high validity and reliability [56, 57]. The accelerometer will be used to objectively define the participants levels of physical activity at baseline, post-treatment, and 6-month follow-up.

The New General Self-Efficacy Scale (S-GSE) is an 8-item measure with a 4-point scale that assesses self-efficacy, that is how much people believe they can achieve their goals, despite difficulties [58]. Higher scores indicate a higher degree of self-efficacy.

Functional impairment will be assessed with the World Health Organization (WHO) Disability Assessment Schedule 12-item (WHODAS-12), a self-rating scale with 12 items [59]. Higher scores indicate greater functional impairment.

The Brunnsviken Brief Quality of life scale (BBQ) measures importance-adjusted satisfaction and has been recommended for use in psychological and psychiatric research and practice [60]. The BBQ is a self-administered questionnaire using 12 questions to address six areas: Leisure time, View on life, Creativity, Learning, Friends and Friendship, and View of self. Health-related quality of life and estimation of quality-adjusted life years (QALY) for health economic evaluations will be measured using the EuroQol-5 Dimensions-5 Level Scale (EQ-5D) [61], a 5-item scale measuring health status with regards to mobility, self-care, usual activities, pain/discomfort, and anxiety/depression.

## Sample size

A total of 250 participants will be included in the trial. Sample size calculation is based on a previous meta-analysis of Behavioural Activation in older adults with mean effect sizes of 0.72 at post-treatment and 0.44 at follow-ups at 3–6 months [21], which is in line with our pilot study of telephone-based BA for older adults yielding an effect size of 0.85 at post-treatment [38] and 0.41 at 6 months post-treatment [44]. An effect size of 0.4 was chosen, based on previously mentioned meta-analysis and pilot study but also following recommendations on the lower value for an effect size corresponding to a medium-sized effect in gerontological research [62]. According to G*Power, 250 participants are needed in total to achieve 80% power with a significance level of 0.05 and a drop-out rate of 20% for analysis of co-variance, ANCOVA. The flow of this study will follow the Modified CONSORT Statement extension for individual randomised controlled trials of non-pharmacological treatments (Fig. 2) [63].

**Fig. 2 Fig2:**
[figure not shown]
Modified CONSORT flow diagram for individual randomised, controlled trials of nonpharmacologic treatment

## Retention

A text message reminder will be sent to the potential participant 1 day before the clinical assessment. The participants will receive a timeline illustrating the different components of their participation in the study; an updated version of the timeline with the addition of an instruction letter for the assessments will be provided at each follow-up. The participants will be reminded of the questionnaires and the accelerometer during the telephone interview at post-treatment and 6-month follow-up.

Each healthcare centre will have a contact person representing the study. The contact person will visit the healthcare centre regularly to answer questions and remind the GPs about the trial. Posters will be put up in staff areas as a reminder and GPs will receive notepads listing the required participant information and complete inclusion/exclusion criteria to facilitate recruitment of eligible participants.

## Data management

All data forms and data files will be pseudonymised, and the code key will be stored separate. Access to the code key is restricted to researchers in the research group and study therapists taking part in initial assessment and treatment. All data will be managed using Vesta, a secure storage for research data provided by Uppsala university. If a participant chooses to discontinue their participations in the study, all the information up until then is used in the analyses but no additional information is collected.

The PI and study coordinator are certified in Good Clinical Practice (GCP), and the enrolled Ph.D. students has also been trained in GCP. General Data Protection Regulation (GDPR) and necessary agreements will be ensured according to the routines at the Centre for Clinical Research in Region Västmanland and Uppsala university. The research group, consisting of the PI, Ph.D. students, and their supervisors, will attend monthly meetings to assure that the data collection is conducted in accordance with the study protocol. Additional monitoring of trial progress is not deemed necessary due to a low risk of harm [38].

## Statistical methods

The difference between the intervention group and control group in depressive symptoms post-intervention measured with MADRS-S will be estimated using analysis of covariance (ANCOVA) with baseline values on the MADRS-S as covariate as well as with the between-group effect size post-intervention using Cohen’s *d*. Difference from baseline between the groups post-intervention and long-term follow-ups (3 and 6 months) will be analysed separately with repeated measures ANOVA. All continuous secondary outcome measures will be estimated using ANCOVA and repeated measures ANOVA, whereas discrete outcomes (i.e. depression diagnosis) will be estimated using logistic regression. Attrition will be analysed using *T*-test for continuous measures (age, depression severity on the MADRS-S, cognitive functioning on the MMSE and FAB-Swe) and chi-square for sex. Analyses will be conducted both using intention-to-treat (ITT) as a primary analysis and per-protocol as a secondary analysis. In the ITT, all randomised participants will be included, whereas only participants that adhered to the treatment or control-condition will be included in the per-protocol analyses. Missing data will be handled by using multiple imputation. Stopping guidelines for trial termination due to negative effects is not applicable and no interim analyses are planned.

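### MADRS-S at 3 and 6 months is assigned to repeated measures ANOVA on the difference from baseline, so the 80% power stated for ANCOVA does not carry over automatically to those visits

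*Protocol article*

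**What the plan says.** The Methods part of the Abstract lists three time points for the primary outcome, MADRS-S: after treatment, 3 months and 6 months.

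Sample size states "A total of 250 participants will be included in the trial" and gives the powered test as one "for analysis of co-variance, ANCOVA", with 80% power, significance level 0.05 and 20% drop-out. On the effect size it says: "An effect size of 0.4 was chosen, based on previously mentioned meta-analysis and pilot study". The sources reported there are a meta-analysis with "mean effect sizes of 0.72 at post-treatment and 0.44 at follow-ups" and a pilot with 0.85 post-treatment and "0.41 at 6 months post-treatment".

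Statistical methods uses ANCOVA with baseline MADRS-S as covariate for the post-intervention comparison. The next sentence takes the difference from baseline post-intervention and at the 3- and 6-month follow-ups, and says that these "will be analysed separately with repeated measures ANOVA". For the other scales it says: "All continuous secondary outcome measures will be estimated using ANCOVA and repeated measures ANOVA". Missing data are to be multiply imputed.

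**The concern.** The power statement and the lead post-intervention analysis both rest on ANCOVA. At 3 and 6 months, which are also primary time points, the only method named for MADRS-S is a different one, and no power, SD or within-person correlation is given for it.

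The design effect of 0.4 lies next to the follow-up estimates (0.44 and 0.41) and well below the post-treatment estimates (0.72 and 0.85). Post-treatment therefore has ample margin and follow-up has little. The less efficient test is placed where precision matters most.

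There is a second, smaller issue. The repeated measures sentence also covers post-intervention, so MADRS-S has two between-group analyses at that visit, and the continuous secondary outcomes are assigned both methods. The two can disagree when baseline means differ by chance, and nothing says which result prevails.

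**Working it through.** **1. The plan's own figure.** Inputs from Sample size: effect 0.4 (Cohen's f = 0.4/2 = 0.2 for two equal groups), power 80%, alpha 0.05 (two-sided assumed), drop-out 20%. For an ANCOVA F-test with 1 numerator df, two groups and one covariate, the noncentrality is λ = N·f². The smallest N reaching 80% is 199 (λ = 199 × 0.04 = 7.96, power 0.802). Then 199/(1 − 0.20) = 248.75, so 249. The stated 250 is reproduced for ANCOVA. A one-sided test would give 195 and does not fit.

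**2. What the follow-up test is.** With baseline and one follow-up, the group-by-time F-test is the square of a two-sample t-test on change scores. Let r be the baseline-to-follow-up correlation and k the ratio of follow-up SD to baseline SD. In units of the follow-up variance:
- change score: 1 + 1/k² − 2r/k
- baseline-adjusted ANCOVA: 1 − r²

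The first equals (1/k − r)² + (1 − r²), so it is never smaller than the second. With equal SDs (k = 1) it becomes 2(1 − r), and the ratio of the two variances is 2/(1 + r).

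**3. Power at one follow-up visit.** Assumptions: 200 completers (250 × 0.8), 100 per arm, d = 0.4 on the raw SD, k = 1, alpha 0.05 two-sided. The values of r are assumed. The t noncentrality is 0.4·√(100/2) = 2.828, divided by the square root of the variance factor.

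| r | Factor, change | Factor, ANCOVA | Variance ratio | Power, change | Power, ANCOVA | Total N for 80% by change score, with drop-out |
|---|---|---|---|---|---|---|
| 0.3 | 1.40 | 0.91 | 1.54 | 66% | 84% | 345 |
| 0.4 | 1.20 | 0.84 | 1.43 | 73% | 87% | 295 |
| 0.5 | 1.00 | 0.75 | 1.33 | 80% | 90% | 248 |
| 0.6 | 0.80 | 0.64 | 1.25 | 88% | 94% | 198 |

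**4. Sensitivity to the SD ratio.** The change-score factor is 1, giving about 80% power, when r = 1/(2k). That is r = 0.50 at k = 1, 1/2.5 = 0.40 at k = 1.25, and 1/1.6 = 0.625 at k = 0.8.

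**5. Sensitivity to the meaning of 0.4.** The article does not say whether 0.4 is on the raw or the baseline-adjusted SD. If adjusted, and k = 1, the change-score effect is 0.4·√((1 + r)/2). Power is then 62% at r = 0.3, 65% at 0.4, 68% at 0.5 and 71% at 0.6, while ANCOVA stays at 80%.

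**6. If one four-occasion model is meant.** The group-by-time test then has 3 numerator df. Assume compound symmetry and a constant 0.4 after baseline. The group differences are (0, 0.4, 0.4, 0.4), with mean 0.3 and sum of squared deviations 0.09 + 3 × 0.01 = 0.12. So λ = (100/2) × 0.12/(1 − r) = 6/(1 − r), with 3 and 594 df. Power is 68% at r = 0.3, 84% at r = 0.5 and 97% at r = 0.7. This too depends on an unstated correlation.

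**The case against.** The strongest reply is that nothing stated is wrong. Sample size names ANCOVA, the lead analysis is ANCOVA post-intervention, and 250 is correct for it. The article does not claim 80% power for the repeated measures ANOVA. A change-from-baseline comparison is unbiased under randomisation, so what remains is efficiency. This stands, and it limits the point: the sample size is not in error.

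A reader might infer that follow-up is underpowered whenever r is below 0.5. The article does not support that. The threshold holds only for equal SDs and an effect on the raw SD. Entry requires a depressive disorder and excludes severe depression, which may narrow the baseline spread; k above 1 is then plausible and lowers the threshold.

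A reader might also object that repeated measures ANOVA needs complete cases, or that its F-tests pool awkwardly after imputation. Neither carries weight here. Multiple imputation supplies completed data sets, and a one-df change contrast pools directly by Rubin's rules. Pooling is more awkward only for a multi-df test.

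The word for separate analysis is ambiguous between one model per visit and one model distinct from the ANCOVA, and a fuller plan may settle the layout. Steps 3 and 6 show that power depends on r under both.

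Finally, the overlap of methods for MADRS-S exists only post-intervention; at 3 and 6 months one method is named. For the secondary outcomes, the sentence could be read as mirroring the primary outcome, with ANCOVA post-treatment and repeated measures ANOVA over follow-up. That reading is possible, but the text does not say so and gives no order of precedence.

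**Conclusion.** The point holds as a mismatch between the powered method and the method assigned to two of the three primary time points. The 250 participants and 80% power are right for ANCOVA and cannot simply be read across to 3 and 6 months.

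Under 200 completers, d = 0.4 on the raw SD and equal SDs, the change-score test gives up 18 percentage points of power at r = 0.3 (84 − 66), 10 at r = 0.5 (90 − 80) and 6 at r = 0.6 (94 − 88). It reaches 80% from r of about 0.5. If 0.4 is the adjusted effect, it stays below 80% across the values of r in step 5, again with equal SDs.

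The conclusion that the trial is underpowered at follow-up goes further than the article allows, because r, the SD ratio and the scale of the 0.4 are not given. What can be said without them is that ANCOVA at the same visits is asymptotically never less precise. The lack of precedence between the two methods is a real but smaller gap, confined to MADRS-S post-intervention and the continuous secondary outcomes.

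**What to change.** In Statistical methods, replace the repeated measures ANOVA by the baseline-adjusted ANCOVA already planned post-intervention. Apply it to the multiply imputed data at post-treatment, 3 months and 6 months for MADRS-S, and at each measured visit for the continuous secondary outcomes. State that this is the one between-group analysis per outcome. A baseline-adjusted mixed model reporting the arm difference at each visit is an acceptable alternative; choosing it over visit-wise ANCOVA is largely preference.

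If the repeated measures ANOVA is kept, say whether it is one model per visit or one model over all visits, give its power with the assumed correlation and SDs, and state which result prevails where both methods apply.

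No new data, visits or participants are needed. Recruitment is planned to run to June 30, 2027, so there is time to make the change. The cost is a text change and, if it is judged an important modification, the ethics application and registry update described under Trial status.

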## Harms

No serious adverse events (SAEs) were reported in the pilot trial [38]. There is no anticipated harm and compensation for trial participation. The study therapists will continuously evaluate the participants' condition and suicide risk at each treatment session in the treatment group. We will adhere to the local guidelines for elevated suicide risk in primary care. Serious adverse events will be reported to the research team immediately after obtaining knowledge about them. Any harms reported to the research team will be described in future trial publications.

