## Interventions

### Treatment group

The treatment group will receive TAU with the addition of a five-session telephone-based BA-intervention over an 8-week period. The telephone-based BA-intervention is based on a treatment protocol called Behavioural Activation for Primary Care, BA-PC [42, 43], that was translated and adapted to Swedish by our research group and subsequently used in a pilot study of BA in isolated older adults with depression during the COVID-19 pandemic [38, 44]. Fourteen of the participants were interviewed on their experiences of the treatment [45], and one suggestion from several of the participants was to add one follow-up call, a so-called booster session. Another suggestion that has been implemented in this version of the treatment is to conduct the first treatment session in-person.

In the planned study, the treatment will consist of five treatment sessions, with sessions 1 through 4 conducted once a week and session 5 conducted 4 weeks after session 4. Session 1 will be conducted in-person, and the following sessions will be conducted by telephone. The estimated session length is 45–60 min for session 1 and 30–45 min for sessions 2 through 5. The session outline is described in Table 1. There will be no special criteria for discontinuing or modifying allocated interventions.

**Table 1 Tab1:** Session outline for the BA treatment

Session no	Session components
1	Present the treatment materials Assess mood and suicide risk Provide psychoeducation about depression Provide treatment rationale for behavioural activation (BA) Provide rationale and instructions for activity log If highly motivated for change, plan activity for coming week
2	Follow-up on mood and suicide risk Review activity log Discuss life goals and values Plan activities aligned with life goals and values for coming week
3	Follow-up on mood and suicide risk Review activity log Troubleshoot any problems carrying out activities Plan activities aligned with life goals and values for coming week
4	Follow-up on mood and suicide risk Review activity log Troubleshoot any problems carrying out activities Plan activities aligned with life goals and values for coming week Instruct the participant to independently plan activities aligned with life goals and values until the booster session
5	Follow-up on mood and suicide risk Review activity log Troubleshoot any problems planning or carrying out activities Review treatment Create a maintenance plan

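### Condition and suicide-risk checks are described only at the five BA sessions, so harm counts described by arm would not be comparable

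*Protocol article*

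**What the plan says.** The Harms section of the protocol article says that study therapists continuously evaluate participants' "condition and suicide risk at each treatment session in the treatment group". Table 1 agrees: mood and suicide risk are assessed in session 1, and the entry "Follow-up on mood and suicide risk" stands in sessions 2 to 5. The Treatment group section sets the timing: "five treatment sessions, with sessions 1 through 4 conducted once a week and session 5 conducted 4 weeks after session 4".

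The other statements on harms are not tied to an arm:
- SAE route: "Serious adverse events will be reported to the research team immediately after obtaining knowledge about them".
- Elevated suicide risk: "We will adhere to the local guidelines for elevated suicide risk in primary care".
- Output: "Any harms reported to the research team will be described in future trial publications".

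The Control group section describes guideline-based care and mentions no study contact between baseline and the post-treatment assessment. The Statistical methods section contains no harms analysis.

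**The concern.** In the BA arm, study staff have five scheduled occasions during treatment on which they ask about the participant's state. In the TAU arm, none is described for the same period. An event there reaches the research team when somebody learns of it and passes it on, for example a GP, who is not blinded. Later publications are to describe whatever harms were reported, and in a two-arm trial readers will set the arms side by side.

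An excess in BA could then be a detection effect alone, and a low TAU count could mean only that fewer questions were asked. Neither would support a statement on safety in depressed older adults. Events that nobody asked about at the time are hard to recover in later analysis.

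**Working it through.** **Step 1. Scheduled enquiries described, by arm**

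| Contact (section of the article) | BA | TAU | Described as harms enquiry? |
|---|---|---|---|
| Therapist check at sessions 1 to 5 (Harms; Table 1) | 5 | 0 | Yes, condition and suicide risk |
| SAE reporting once known (Harms) | yes | yes | Passive |
| MADRS-S at post-treatment, 3 and 6 months (Abstract) | 3 | 3 | No, primary outcome |
| MINI depressive episode module by telephone, post-treatment and 6 months (Secondary outcomes) | 2 | 2 | No, secondary outcome |

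The five sessions fall within the 8-week period: session 4 comes 3 weeks after session 1, and session 5 comes 3 + 4 = 7 weeks after session 1. The count during treatment is therefore 5 against 0.

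**Step 2. Effect of unequal detection**

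The article gives no harms figure to reproduce. Let *p* be the true event risk, equal in both arms, and let *s*(BA) and *s*(TAU) be the probabilities that an event is recorded. Then

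recorded risk = *p* × *s*

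apparent risk ratio = [*p* × *s*(BA)] / [*p* × *s*(TAU)] = *s*(BA) / *s*(TAU)

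The true risk cancels, so the distortion depends only on the ratio of the detection probabilities.

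**Step 3. Numbers**

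From the article: 250 participants allocated 1:1, so 250 / 2 = 125 per arm. Assumed, because the documents give no such figures: true risk 5%, detection 90% in BA, and detection from 90% down to 30% in TAU.

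| Detection in TAU | Apparent ratio | Expected recorded, BA | Expected recorded, TAU |
|---|---|---|---|
| 90% | 0.9 / 0.9 = 1.0 | 125 × 0.05 × 0.9 = 5.6 | 125 × 0.05 × 0.9 = 5.6 |
| 70% | 0.9 / 0.7 = 1.29 | 5.6 | 125 × 0.05 × 0.7 = 4.4 |
| 50% | 0.9 / 0.5 = 1.8 | 5.6 | 125 × 0.05 × 0.5 = 3.1 |
| 30% | 0.9 / 0.3 = 3.0 | 5.6 | 125 × 0.05 × 0.3 = 1.9 |

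At a true risk of 2%, the expected BA count is 2.25, against 2.25 down to 0.75 in TAU. At 10% it is 11.25, against 11.25 down to 3.75. The ratios are the same.

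**Step 4. What is already symmetric**

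MADRS-S is measured on the same schedule in both arms, so worsening from baseline can be counted without this problem. The same holds for depression diagnosis on the MINI module. Other adverse events and SAEs have no such common source in the article.

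**The case against.** The strongest objection is that no analysis is harmed. The article plans no test or estimate comparing harms between arms; it only says that harms will be described. This stands, and it limits the point to descriptive counts. It does not remove the point, because unequal ascertainment distorts a plain count as much as a tested one.

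A reader might infer that TAU events go unseen. The text does not support that. SAE reporting is not restricted to an arm, TAU participants remain with their GPs under the local guidelines, and both arms are assessed at post-treatment, 3 and 6 months. Less likely to be seen is as far as the text goes. Nor is deterioration in depression hidden, since MADRS-S records it in both arms.

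A reader might also take "Additional monitoring of trial progress is not deemed necessary due to a low risk of harm", in the Data management section, to mean that nothing could catch the imbalance. That sentence follows one on monthly meetings about adherence to the protocol in data collection. It concerns oversight of the trial and does not say how harms are elicited in each arm.

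Finally, the article is condensed, and the full protocol may hold an adverse-event form used in both arms. That is possible, and the article does not say that the therapists' checks are the only ascertainment. However, the Harms section itself describes a scheme and words its active part for one arm. The point rests on that wording and not on silence alone.

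**Conclusion.** The point holds in a limited form. As described, active checks number five in BA and none in TAU during treatment, and the remaining route is passive. Harm counts described by arm are therefore not comparable. If detection is lower in TAU, which is the likely direction, BA will look worse than it is.

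The size cannot be fixed from the documents. Under the assumed detection range, the apparent risk ratio with no true difference lies between 1.0 and 3.0. The lower end means no bias, and no single value in between deserves weight. The calculation assumes equal true risks and 125 participants per arm; the ratio depends on neither the 125 nor the level of risk.

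It would go too far to call a planned harms comparison biased by design, since none is planned, or to say that no safety conclusion at all can be drawn, since MADRS-S worsening is measured in the same way in both arms. The primary efficacy analysis and the sample size are unaffected. The change is still worth making, because unasked events are hard to recover afterwards.

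**What to change.** 1. Add the same short adverse-event and SAE questions for both arms to the existing self-administered questionnaires at post-treatment, 3 and 6 months. The telephone interviews, mentioned in the Retention section ("during the telephone interview at post-treatment and 6-month follow-up"), look like the obvious place. But answers may hint at allocation, and a blinded interviewer who hears them at post-treatment could carry that into the 6-month MINI. If the questions are to be asked orally, someone other than the blinded interviewer should ask them.
2. State that any description of harms by arm uses only these symmetric data, and list events detected at BA sessions separately.
3. Report MADRS-S worsening from baseline by arm, using data already collected.
4. Leave the checks at the BA sessions as they are. The change concerns data collection and reporting only.

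**Cost.** A few extra questions at each follow-up, plus a protocol modification. If the modification counts as important, the Trial status section requires a further application to the ethics authority and a change to the registration. Recruitment began in March 2024, so participants already past a follow-up will lack the new data for that time point; MADRS-S worsening remains available for them. The publication should say from when the questions were asked. If the full protocol already collects harms identically in both arms, items 2 and 3 and a sentence saying so are enough.
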